### Sample size calculation

The sample size was based on the only previous randomized controlled trial that we found that measured changes in physical activity levels of people with stroke associated with aerobic exercise training [16]. The effect size was derived from the study of Teixeira-Salmela et al. [19], who assessed changes in physical activity levels with HAP Adjusted Activity Scores that were associated with aerobic plus lower-limb strengthening training and home exercises, for people with chronic stroke. In that study, the experimental group (*n* = 6) showed an average increase in Adjusted Activity Score of 20 ± 6.1 after the intervention, whereas the control group (*n* = 7) had an average reduction of 1.86 ± 0.19 points. To be able to detect a between-group difference of 20 points on the HAP Adjusted Activity Score, considering a significance level of 5% and a desired power of 80%, nine participants per group are required (a total of 18 participants) [46]. Assuming an expected dropout rate of 20%, a target of 22 participants was set (11 participants per group).

### Statistical analyses

Each participant will be assigned a unique ID. Two independent examiners, who will be blinded to the group allocation, will enter the data into a computer and verify any missing or apparently wrong values. The original paper forms will be kept in a secure place. The electronic files will be available only to the research team.

An independent examiner, who will be blinded to group allocation, will perform the statistical analysis, using the software SPSS (SPSS Inc., Chicago, IL, USA). Descriptive statistics will be calculated for all outcomes.

The effects of the interventions will be analyzed from the collected data using intention to treat. Data from the last available assessment will be used for missed sessions. Between-group differences will be evaluated using two-way repeated measures ANOVA, considering the baseline, post-training, and follow-up measurements. If there are baseline differences between the groups, analysis of covariance will be used to eliminate the influence of extraneous factors, such as baseline cardiorespiratory fitness, physical activity levels, and time spent in low-energy expenditure activities. The level of significance will be set at 5% and adjusted for multiple comparisons. Data distribution and equality of variance will also be analyzed, to ensure the parametric analysis has been applied correctly.

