Investigating the influence of exercise on physical activity levels and the importance of reducing the time spent in low-energy expenditure activities in people with stroke has been suggested in a scientific statement from the American Stroke Association as a future research direction [3]. Any exercise would probably increase physical activity level and reduce sedentary duration on the same day that it is performed. However, it is not known which intervention could effectively improve physical activity. In addition, it is also unknown whether these changes occur in individuals with different baseline levels of physical activity and time involved in low-energy expenditure activities, nor if they are maintained after the cessation of the intervention. Since the efficacy of aerobic training in improving cardiorespiratory fitness in people with stroke has been shown [8–10] and that cardiorespiratory fitness is a significant predictor of physical activity after stroke [15], it may be important to investigate whether aerobic training is effective in increasing physical activity levels and reducing the time spent in low-energy expenditure activities in this population. However, the efficacy of aerobic training on these variables is not well known [3, 9].

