## Methods/design

A superiority parallel-group randomized controlled trial, with concealed allocation and blinded assessments, will be carried out. A trained researcher, blinded to the group allocation, will collect the written consent and the outcome measures at baseline, post-intervention (after the 12-week intervention), and at the 16-week follow-up, i.e., 4 weeks after the cessation of the intervention (Fig. 1). The examiner will be blinded to group allocation, and the participants and the treating physiotherapist will be asked not to share any information about the intervention with the examiner. Moreover, evaluations will be carried out in different places. Participants will be randomly assigned to either (1) aerobic treadmill training (experimental group) or (2) walking outside (control group) (Fig. 2).

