### Participant withdrawal

Participants may withdraw from the trial for any reason at any time. The investigator can withdraw participants from the study for safety purposes. Missing a maximum of six consecutive sessions will be allowed.

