### Randomization procedures

The randomization sequence will be computer generated prior to the commencement of the study by a trained research assistant, who will be not involved in the study, and maintained in randomized blocks in sequentially numbered sealed opaque envelopes. Eligible participants will be randomly allocated to either the experimental or control group, after the baseline measurements. The training therapist will be responsible for revealing the contents of the sealed opaque envelopes, and therefore, for revealing the allocation.

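### The plan's only missing-data rule carries the last assessment forward, which can shrink the post-training effect, move the follow-up effect either way, and understate any loss of effect between the two

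*Protocol article*

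**What the plan says.** The Statistical analyses section commits to intention to treat ("The effects of the interventions will be analyzed from the collected data using intention to treat") and follows it with the only missing-data rule in the article: "Data from the last available assessment will be used for missed sessions". The between-group comparison is a two-way repeated measures ANOVA, "considering the baseline, post-training, and follow-up measurements". No sensitivity analysis for missing data is named.

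Three other sections determine what the rule does in practice:

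- Randomization procedures: "Eligible participants will be randomly allocated to either the experimental or control group, after the baseline measurements". Everyone randomised therefore has a baseline value that can be carried forward.
- Methods/design: after baseline, outcomes are measured at week 12 and at week 16, the latter "4 weeks after the cessation of the intervention".
- Sample size calculation: loss is anticipated ("Assuming an expected dropout rate of 20" per cent), with no timing and no split by arm.

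The Background lists as unknown whether changes in activity occur at different baseline levels, "nor if they are maintained after the cessation of the intervention".

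**The concern.** With three assessments, the rule acts in two ways. A participant with no week-12 value receives the baseline value, so the change is set to exactly zero. A participant who attends week 12 but misses week 16 receives the week-12 value, so the loss of effect is set to exactly zero. In both cases the analysis counts an assumed value as a measured one, and the standard error ignores that.

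The first action affects the estimate on which the efficacy claim rests. The second bears on persistence after training stops, which the article itself calls unknown: for those missing only the last visit, the rule supplies the answer. The follow-up effect can come out too large or too small, depending on when people leave and how much of the effect truly remains.

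**Working it through.** **Inputs from the article** (Sample size calculation): 18 evaluable participants (nine per group), a 20-point difference on the Human Activity Profile adjusted score, 20% dropout, 22 randomised (11 per group). The source study's mean changes were +20 (experimental) and -1.86 (control).

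**Assumptions not in the article:** dropout equal by arm and unrelated to outcome; its timing; the share of the effect retained at week 16. For rejection rates only: a change-score SD of 14.3 and a between-visit correlation of 0.6.

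**The plan's own figure.** 18 × 1.2 = 21.6, rounded up to 22, reproduces the target. (Dividing instead, 18 / 0.8 = 22.5, gives 23.) Twenty per cent of 11 is 2.2, or about two people per arm.

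**Expected estimates under the rule.** Let δ = 20 be the true post-training difference, e the share missing both later visits, f the share missing week 16 only, and r the share of δ truly retained at week 16 (0 to 1).

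- Post-training: (1 - e) × δ
- Follow-up: [(1 - e - f) × r + f] × δ
- Fall between the visits: (1 - e - f) × (1 - r) × δ

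| Timing of the 20% loss | e | f | Post-training (true 20) | Follow-up (true 0) | Follow-up (true 10) | Follow-up (true 20) |
|---|---|---|---|---|---|---|
| All before week 12 | 0.20 | 0 | 16 | 0 | 8 | 16 |
| Split evenly | 0.10 | 0.10 | 18 | 2 | 10 | 18 |
| All after week 12 | 0 | 0.20 | 20 | 4 | 12 | 20 |

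Examples: 0.90 × 20 = 18; (0.80 × 0.5 + 0.10) × 20 = 10; (0.80 × 0 + 0.20) × 20 = 4.

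**Direction at follow-up.** The bias is [f - (e + f) × r] × δ. With e + f = 0.20 it runs from -4 (f = 0, r = 1) to +4 (f = 0.20, r = 0). It is upward only if r < f / (e + f), which is r < 0.50 for an even split.

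**Fall between visits.** Here 1 - e - f = 0.80 whatever the timing, so a true fall of 20 is estimated as 16 and a true fall of 10 as 8.

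**Source-study means.** The true difference would be 20 + 1.86 = 21.86. With all loss before week 12, the rule gives 0.80 × 21.86 = 17.49.

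**Error rates.** These come from 20,000 simulated trials per scenario, 11 per arm, with a t-test on change from baseline:

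- True follow-up effect 0, all loss after week 12: rejection rate 8.8% under the rule, 4.9% with observed data only.
- True follow-up effect 0, even split: 5.7% against 4.9%.
- True post-training effect 20, all loss before week 12: power 0.73 under the rule, 0.78 with observed data, 0.88 with nothing missing.

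Simulations with ANCOVA, SD 14.2 and correlation 0.5 gave 9.0% to 9.7% for the first scenario. For the third, coverage of the 95% interval was 89%, against 95% with observed data. None of these is the planned repeated measures ANOVA, so they indicate size only. The expected values in the table need no SD or correlation.

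**The case against.** **A stronger reading.** A reader might infer that the rule necessarily biases both comparisons and manufactures a maintained effect at follow-up. The article does not support that. It gives one dropout figure without timing, and the post-training estimate of 16 and the follow-up inflation of 4 each use up the whole 20%, so one trial cannot show both. If all loss follows week 12, the post-training comparison is unbiased. If all loss precedes week 12, a true follow-up effect of 0 is estimated as 0. With an even split and half the effect retained, the follow-up estimate is exactly right at 10.

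**The benchmark assumes dropouts would have benefited.** If those who leave before week 12 gain nothing, the intention-to-treat effect is 0.80 × 20 + 0.20 × 0 = 16. The rule then gives 16, and an analysis of observed data gives 20. This stands. It means the replacement needs a sensitivity analysis, but it does not justify the rule, which is right there only because its assumption happens to hold.

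**Wording.** The rule speaks of sessions, a word used for training attendance under Participant withdrawal ("Missing a maximum of six consecutive sessions will be allowed"). Since an assessment can only stand in for another assessment, missed assessments is the sensible reading, but the text is loose. Dropout from training also need not mean missing outcomes.

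**Scale.** About two people per arm are affected. With equal dropout and no effect at either visit, the rule creates no mean difference. Persistence is raised in the Background and is not part of the stated primary aim. These points limit severity.

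**A separate analysis plan.** One may exist, but the article does not leave the method open: it states a rule, and that rule is the problem.

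**Conclusion.** The point holds in conditional form. The article's only missing-data rule is single imputation by last observation carried forward. It can pull the post-training effect toward zero, by up to 4 of 20 points. It can move the follow-up effect by anything from -4 to +4 points. Whenever there is a real loss of effect between weeks 12 and 16, the rule understates it by the share missing at week 16, which is one fifth here. The type I error at follow-up reaches about 9% only if the true effect there is 0 and all loss falls after week 12, with an assumed SD near 14 and correlation of 0.5 to 0.6.

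All of these figures assume dropout unrelated to outcome and equal by arm. Because the timing cannot be known in advance, the direction of the follow-up bias cannot be either, so the rule cannot be defended as conservative. Severity: should-fix.

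**What to change.** 1. Replace the rule with a likelihood-based linear mixed model on all observed visits (SPSS MIXED, REML, small-sample degrees of freedom). Treat baseline, week 12 and week 16 as outcomes and constrain baseline means to be equal across groups, which is justified because baseline is measured before allocation. Estimate the group difference at each later visit. Baseline must be an outcome: if it were only a covariate, anyone with no later value would drop out of the model, and not every randomised participant would contribute in the assigned group. Deleting the rule while keeping the classical repeated measures ANOVA would not do either, since that method needs all three values per person.
2. Add a sensitivity analysis for informative dropout, for example one in which dropouts are assumed to gain no benefit.
3. Keep last observation carried forward at most as a further sensitivity analysis.
4. Change missed sessions to missed assessments.

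The cost is analysis wording only, in software the article already names, with no new visits or data. Recruitment was still under way according to Trial status, so the change could precede the analysis. The one downside is that the mixed model assumes data are missing at random and would overstate the intention-to-treat effect if dropouts truly gain nothing; step 2 covers that case.

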## Discussion

Although the efficacy of aerobic training in improving VO_2peak_ in individuals with stroke is well known, it is unknown if this training improves physical activity levels and reduces the time spent in low-energy expenditure activities. In fact, it is still unclear which interventions can improve physical activity levels and reduce time spent post-stroke in low-energy expenditure activities. Therefore, the results of this randomized controlled trial will likely provide valuable new information regarding the effects of aerobic treadmill training on physical activity levels and time spent in low-energy expenditure activities for individuals with stroke. Since low levels of physical activity are associated with risk of cardiovascular disease, the investigated intervention may help to improve functionality and health status and reduce the burden of care on the families of people with stroke. Whether exercise improves function and quality of life and prevents secondary diseases, such as stroke, is a high priority research objective, which may be answered by this study [47].

Considering that previous randomized controlled trials have rarely investigated the effects of aerobic training on physical activity levels and that none have investigated these effects on the time spent in low-energy expenditure activities or have used a multi-sensor monitor to measure these outcomes, this study may increase the use of evidence-based practice in that domain, and, hence, may improve the care of people with stroke.

This trial design does have some limitations. It will include a convenience sample, which may limit generalizability. Furthermore, both the participants and the physiotherapist, who will provide the interventions, will not be blinded (Additional file 1).

### Trial status

Protocol version: 1

Trial registration: ClinicalTrials.gov

Registration number: NCT02798237.

Date of trial registration: 13 June 2016

Was this trial prospectively registered? Yes

Date recruitment began: August 2017. Recruiting is ongoing

Anticipated completion date: December 2018

## Abbreviations

6MWT: Six-minute walk test
HAP: Human Activity Profile
MET: Metabolic equivalent
PHQ: Patient Health Questionnaire
SIS: Stroke Impact Scale
SSQOL: Stroke-Specific Quality of Life Scale
SWT: Shuttle-walk test
VO_2peak_: Peak oxygen uptake
